### Questionnaires

At different time-points, questionnaires will be provided. The first questionnaire is sent after the prior consultation to all subjects scheduled for the screening test to assess the following items: demographic and socioeconomic status, satisfaction of the prior consultation, reasons for participation, level of informed choice and expected burden of the screening procedure (items 1-5, see below). The same questionnaire is sent to all subjects not responding to the first invitation (non-respondents), together with the reminder, and to all non-participants to obtain information about the reasons of non-participation. In case of low response, 10% of non-respondents will be contacted by telephone to assess a shortened version of this questionnaire. A second questionnaire is sent to participants two weeks after the screening test and will contain questions about the perceived burden of the screening method (item 5).

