#### 1) Demographic and socioeconomic status

Baseline characteristics as age, gender, marital status, ethnicity, education and employment will be collected.

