### Data analysis

We will calculate the participation rate as the number of participants undergoing the screening test relative to the total number of all eligible invitees. We will compare the participation rate between the three screening programmes, and express it as relative participation rates, calculating corresponding 95% confidence intervals, using colonoscopy screening with a prior consultation at the outpatient clinic as the reference strategy.

We will test the null hypothesis of no difference in participation rate using chi-square test statistics. We will also calculate a conditional relative participation rate using logistic regression modelling, accounting for baseline variables. If the overall hypothesis of no difference is rejected, we will test the null hypothesis of a difference in mode of invitation to direct colonoscopy. Additionally, we will test the null hypothesis of no difference in participation between CT colonography screening and direct colonoscopy screening.

The detection rate of the screening test is defined as the proportion of screenees with detected advanced neoplasia. Advanced neoplasia comprises all carcinomas and advanced adenomas together. An advanced adenoma is defined as an adenoma ≥ 10 mm, with villous histology (≥25% villous) or with high grade dysplasia. The most advanced detected lesion per screenee will be used to calculate the detection rate.

The diagnostic yield per 100 invitees is defined as the proportion of screenees with detected advanced neoplasia relative to all eligible invitees.

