### Sample size

We anticipate a participation rate of 22.5% in colonoscopy screening with a prior consultation at the screening centre, a participation rate of 27.5% with prior consultation by telephone, and a participation rate of 35% in the CT colonography group (based on the participation rate of FS screening in the Netherlands)[17]. Including 7,500 participants in the trial will then achieve a power exceeding 99% to reject the null hypothesis of no difference, using a 2 degrees of freedom Chi-Square test with a significance level set at 0.05.

These numbers will lead to a 98% power to reject subsequently the hypothesis of no difference in participation for the two consultation modes with direct colonoscopy, and a power exceeding 99% for the two other pair wise comparisons between screening programmes.

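### The adjusted relative participation rate is to come from logistic regression, which natively gives an odds ratio; at 22.5–35% uptake the two differ materially and no conversion is stated

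*Protocol article*

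**What the plan says.** All of this is in the Data analysis section of the protocol article unless noted.

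- The outcome is a proportion: "the number of participants undergoing the screening test relative to the total number of all eligible invitees".
- The arms are compared on a ratio of those proportions. The plan is to "express it as relative participation rates, calculating corresponding 95% confidence intervals". The comparator is the colonoscopy arm with the clinic visit.
- The adjusted version follows: "We will also calculate a conditional relative participation rate using logistic regression modelling, accounting for baseline variables". The section does not name the variables or say how the logistic output becomes a relative rate.
- The Sample size section gives the expected uptake: "We anticipate a participation rate of 22.5% in colonoscopy screening with a prior consultation at the screening centre". It puts the telephone arm at 27.5% and the CT colonography arm at 35%.
- The Study design section draws invitees from the municipal register and randomises by household, stratified for age, sex and SES.

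**The concern.** The named measure and the named model do not match. Exponentiating a logistic treatment coefficient gives an odds ratio conditional on the covariates. An odds ratio approximates a ratio of proportions only when the outcome is uncommon in both groups, and uptake of roughly a quarter to a third is not uncommon.

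Two numbers with nearly the same name would stand side by side in the results: an unadjusted ratio of proportions and an adjusted odds ratio. In a randomised comparison the reader expects adjustment to change little. A visible rise would be taken as evidence that baseline imbalance had hidden part of the effect, when only the scale had changed. The Background section calls an evidence-based participation estimate essential for predicting the effectiveness and costs of a programme. A figure read as a ratio of uptakes should therefore be one.

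**Working it through.** **Inputs.** Planned uptake from the Sample size section: 0.225 (colonoscopy, visit), 0.275 (colonoscopy, telephone), 0.35 (CT colonography). Arm size from the Study design section: 2,500 each. The Sample size section places the visit at the screening centre; I take this to be the outpatient-clinic arm.

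**Step 1: the plan's own figure.** Power for 22.5% against 27.5%, two-sided 5%, normal approximation:

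- Standard error under no difference: √(2 × 0.25 × 0.75 / 2,500) = 0.01225
- Standard error under the alternative: √((0.225 × 0.775 + 0.275 × 0.725) / 2,500) = 0.01223
- Power: Φ((0.05 − 1.96 × 0.01225) / 0.01223) = Φ(2.126) = 98.3%

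This agrees with the stated 98%. The other two pairwise powers and the overall 2-df test (noncentrality 97.5) all exceed 99%, as stated. The inputs are therefore read as the authors meant them.

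**Step 2: both measures from the same rates.** With p0 the comparator and p1 the other arm:

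- RR = p1 / p0
- OR = [p1 / (1 − p1)] / [p0 / (1 − p0)]
- OR / RR = (1 − p0) / (1 − p1)
- (OR − 1) / (RR − 1) = 1 / (1 − p1)

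Odds: 0.225/0.775 = 0.2903; 0.275/0.725 = 0.3793; 0.35/0.65 = 0.5385.

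| Comparison | RR | OR | OR / RR | Excess over 1 inflated by |
|---|---|---|---|---|
| CT colonography vs visit | 0.35/0.225 = 1.56 | 0.5385/0.2903 = 1.85 | 0.775/0.65 = 1.19 | 1/0.65 − 1 = 54% |
| CT colonography vs telephone | 0.35/0.275 = 1.27 | 0.5385/0.3793 = 1.42 | 0.725/0.65 = 1.12 | 1/0.65 − 1 = 54% |
| Telephone vs visit | 0.275/0.225 = 1.22 | 0.3793/0.2903 = 1.31 | 0.775/0.725 = 1.07 | 1/0.725 − 1 = 38% |

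**Step 3: compare the gap with the precision.** If the planned rates are observed in 2,500 eligible invitees per arm, ignoring household clustering, the 95% intervals for the RR are:

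- CT colonography vs visit: 1.42 to 1.70
- CT colonography vs telephone: 1.17 to 1.38
- Telephone vs visit: 1.11 to 1.35

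The odds ratios of 1.85 and 1.42 lie outside the first two intervals; 1.31 lies inside the third. For both CT colonography comparisons the change of scale exceeds the sampling uncertainty.

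**Step 4: does the logistic model itself prevent a correct answer?** No. An illustrative simulation used the planned rates with assumed modest effects of age, sex and SES on uptake. The logistic coefficients gave adjusted odds ratios of about 1.32 (telephone) and 1.91 (CT colonography) against the visit arm. With no covariate effects the values are 1.31 and 1.85, as in Step 2. Averaging the predicted probabilities of the same fitted model over all invitees, then taking their ratio, returned about 1.23 and 1.57, close to the true 1.22 and 1.56. The covariate effects are assumptions; the finding rests on Step 2 and does not need them.

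**The case against.** The strongest reply is that the sentence names the target correctly and names only the modelling tool. It does not say that the exponentiated coefficient will be reported. Step 4 shows that logistic regression can deliver a relative rate through marginal standardisation, and a condensed article may leave that step to a fuller document. It is true that the model is not disqualified. But standardisation yields a marginal quantity, and the article calls its result conditional, which points to the coefficient. Followed as written, the sentence puts an odds ratio under a relative-rate label. That is a mismatch between two stated things, not just an omitted detail.

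A second reply is that the analysis is supplementary. This stands in full and limits the weight of the point.

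A reader might also infer something stronger: that the adjustment will use questionnaire items, so that the model loses mainly non-participants. The Questionnaires section does say "Baseline characteristics as age, gender, marital status, ethnicity, education and employment will be collected", and "The first questionnaire is sent after the prior consultation to all subjects scheduled for the screening test". The document does not support the inference:

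- The stratification factors age, sex and SES must be known for every invitee before any response, so questionnaire items are not the only baseline variables described. The Study population section bases the areas and their SES categories on Statistics Netherlands data.
- The Data analysis section does not say that questionnaire items enter the model, and nowhere is an analysis restricted to questionnaire returners planned.
- No return rate is given.
- If return depended on participation alone, the logistic odds ratio would not be distorted by it.

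**Conclusion.** The point holds for the supplementary adjusted estimate. On its natural reading, the plan would report a conditional odds ratio as a relative participation rate. At the protocol's own rates it would show about 1.85 for 1.56, 1.42 for 1.27 and 1.31 for 1.22. These sizes assume that the planned rates occur and that the exponentiated coefficient is what gets reported. If uptake were much lower in all arms the gap would shrink; if higher, it would grow.

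It would go too far to conclude that the primary result is at risk. The chi-square tests, the unadjusted relative rates with their intervals and the sample size calculation do not use the logistic model.

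**What to change.** Replace the sentence on logistic regression with one along these lines: *The adjusted relative participation rate and its 95% confidence interval will be estimated by modified Poisson regression with a log link, with variance robust to clustering within households, adjusting for age, sex and SES.*

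Log-binomial regression, or marginal standardisation of the logistic model with household-level variance, would serve equally. With standardisation, describe the result as marginal rather than conditional. The robust variance is needed because randomisation is per household. Naming the three stratification factors uses variables available for every invitee and settles what the adjustment covers.

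If the authors prefer to report the logistic coefficient, they should label it an adjusted odds ratio and not set it beside the relative rates as the same measure.

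The cost is one sentence, with the same data and standard software. The one practical caution is that log-binomial models sometimes fail to converge; modified Poisson or standardisation avoids this.

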### Sample size

We anticipate a participation rate of 22.5% in colonoscopy screening with a prior consultation at the screening centre, a participation rate of 27.5% with prior consultation by telephone, and a participation rate of 35% in the CT colonography group (based on the participation rate of FS screening in the Netherlands)[17]. Including 7,500 participants in the trial will then achieve a power exceeding 99% to reject the null hypothesis of no difference, using a 2 degrees of freedom Chi-Square test with a significance level set at 0.05.

These numbers will lead to a 98% power to reject subsequently the hypothesis of no difference in participation for the two consultation modes with direct colonoscopy, and a power exceeding 99% for the two other pair wise comparisons between screening programmes.

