CT colonography is a less invasive full colonic exam which can be performed with limited bowel preparation and could therefore be a good alternative in a screening setting [27-29]. CT colonography has been demonstrated to have a high sensitivity for the detection of CRC (96%)[30]. A large screening trial evaluating CT colonography and same day colonoscopy studied 1233 asymptomatic individuals and reported high sensitivity (94%) and specificity (96%) per patient for large adenomas (≥10 mm). Sensitivity and specificity for adenomas larger than or equal to 6 mm was 89% and 80% respectively[31]. The diagnostic yield for advanced neoplasia of CT colonography (3.2%) was comparable to that of colonoscopy (3.4%)[32]. The risk of complications is extremely low, there were no perforations or other serious complications in a large CT colonography screening cohort[32]. CT colonography with limited bowel preparation has a lower burden and is preferred by patients compared to regular CT colonography[33]. A disadvantage of CT colonography is the exposure of individuals to ionizing radiation. However, the chances of radiation induced malignancy are considered very low, especially when a low dose protocol is used. The detection of extracolonic findings in CT colonography could be beneficial, but risks and costs associated with false positives and inconsequential findings may be substantial. Of all available screening tests for CRC, colonoscopy and CT colonography are the most accurate exams.

The optimal screening test for CRC is still a subject of fierce debate. FOBT and FS are suboptimal tests whereas full colonic exams, such as colonoscopy and CT colonography are associated with risks, costs and high workload. An evidence-based estimate of the participation rate is essential for making predictions of the effectiveness and costs of a population screening programme.

In the Netherlands, population based screening trials by gFOBT, iFOBT and FS have already been performed. Studies that investigated stool-based tests as a screening method reported participation rates of 47-50% (gFOBT) and 60-62% (iFOBT)[13,17]. FS-screening had a lower participation rate of 32%[17].

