### Study design

This study will be a two-centre randomized controlled trial. A cohort of 7,500 persons of the Amsterdam and Rijnmond region will be randomly selected from the electronic database of the regional municipal administration registrations (Gemeentelijke Basis Administratie (GBA)). In total, 2,500 persons will be randomly selected to receive an invitation for colonoscopy screening with a prior consultation by telephone. Another 2,500 persons will be randomly selected to receive an invitation for colonoscopy screening with a prior consultation at the outpatient clinic. A third group of 2,500 persons will be randomly selected to receive an invitation for CT colonography, with a prior consultation by telephone [figure 1]. Randomization will be performed per household, stratified for age, sex and socio-economic status (SES).

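### The 35% CT colonography uptake is credited to a Dutch sigmoidoscopy rate that the Background gives as 32%; at 32%, one of the two power claims for CT colonography drops from above 99% to about 94%

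*Protocol article*

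**What the plan says.** The Sample size section of the protocol article gives three planning values:

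- Colonoscopy with a clinic consultation: "We anticipate a participation rate of 22.5% in colonoscopy screening with a prior consultation at the screening centre".
- Colonoscopy with a telephone consultation: "a participation rate of 27.5% with prior consultation by telephone".
- CT colonography: "a participation rate of 35% in the CT colonography group (based on the participation rate of FS screening in the Netherlands", with reference 17 as the source.

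The overall test is specified as "using a 2 degrees of freedom Chi-Square test with a significance level set at 0.05". Study design gives each arm 2,500 invitees. From these inputs the section reports power above 99% overall, 98% between the two consultation modes, and "a power exceeding 99% for the two other pair wise comparisons between screening programmes", meaning CT colonography against each colonoscopy arm.

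The Background, reviewing earlier Dutch pilots, states that "FS-screening had a lower participation rate of 32%[17". The number in brackets is again reference 17.

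**The concern.** The two sections name the same quantity, the same country and the same reference, yet one gives 32% and the other uses 35%. No adjustment is stated. The Discussion expects CT colonography to attract more people than colonoscopy, but does not say that it should attract more than FS. It adds that the further examinations needed after a positive scan could reduce participation in the CT programme as a whole. The article therefore gives a reader no reason to move up from the cited figure.

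Three points matter because the CT value drives both CT power statements. CT colonography against telephone-consultation colonoscopy is the only contrast in which the test differs while the consultation mode is the same. The Background itself hypothesises that consultation mode changes uptake. This is also the CT contrast with the smaller planned difference, so it is the more sensitive to the CT assumption.

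**Working it through.** **Inputs.** n = 2,500 per arm (Study design). Uptake of 22.5%, 27.5% and 35% (Sample size) and 32% (Background). Significance level 0.05. No separate level is stated for the pairwise tests; I assume two-sided 5% with no multiplicity adjustment.

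**Formula for a pairwise comparison** (pooled-variance normal approximation, equal arms):

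- p̄ = (p1 + p2)/2
- SE0 = √[2·p̄(1 − p̄)/n]
- SE1 = √[(p1(1 − p1) + p2(1 − p2))/n]
- power = Φ[(|p2 − p1| − 1.96·SE0)/SE1]

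**Step 1: reproduce the protocol's figures.**

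- 22.5% v 27.5%: SE0 = 0.01225, SE1 = 0.01223; (0.05 − 0.02400)/0.01223 = 2.13; power 98.3% (stated: 98%).
- 27.5% v 35%: SE0 = 0.01311, SE1 = 0.01307; (0.075 − 0.02570)/0.01307 = 3.77; power 99.99% (stated: above 99%).
- 22.5% v 35%: power above 99.99% (stated: above 99%).
- Overall test: noncentrality λ = n·Σ(pi − p̄)²/[p̄(1 − p̄)], with p̄ = 28.33% and Σ(pi − p̄)² = 0.007917, so λ = 97.5; power above 99.99% (stated: above 99%).

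Every stated figure is recovered. The 98% also supports the assumed pairwise level: a one-sided 5% test would give 99.3%, and a Bonferroni level of 0.05/3 would give 95.5%.

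**Step 2: replace 35% by 32%.**

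- 27.5% v 32%: p̄ = 0.2975, SE0 = 0.01293, SE1 = 0.01292; (0.045 − 0.02534)/0.01292 = 1.52; power **93.6%**.
- 22.5% v 32%: (0.095 − 0.02468)/0.01252 = 5.62; power above 99.9%.
- Overall test: p̄ = 27.33%, Σ(pi − p̄)² = 0.004517, λ = 56.8; power above 99.9%.

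**Step 3: does the answer depend on the method?** For 27.5% v 32%, the noncentral chi-square gives 93.6%, unpooled variance 93.6%, and a continuity correction 93.2%. A one-sided 5% test gives 96.7%. None reaches 99%.

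**Step 4: how sensitive is it to the CT rate?** Against 27.5%, power is 93.6% at 32%, 98.9% at 33%, 99.6% at 33.5% and 99.99% at 35%. The published claim thus needs a CT uptake somewhat above 33%. Keeping 99% power at 32% would take about 3,788 per arm.

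**The case against.** Four objections deserve an answer.

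*The powers are right.* A reader might infer from the discrepancy that the power calculation is wrong. It is not: every figure reproduces at the stated inputs, and those inputs are offered as anticipated rates. The fault lies in the stated basis for one input. This objection stands.

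*Being based on a rate does not mean being equal to it.* CT colonography is a different test, and the Background describes it as less invasive and needing only limited bowel preparation, so a planning value somewhat above FS is plausible. A condensed article may also omit the reasoning, and reference 17 cannot be consulted here. A deliberate adjustment therefore cannot be excluded. But the article prints both numbers with the same source and names FS participation as the basis for the higher one. An adjustment needs to be stated, because a reader tracing the source within the article arrives at 32%.

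*Only one claim is affected.* This stands. A reader might infer that both CT power statements fail. CT colonography against outpatient-consultation colonoscopy, which Data analysis makes the reference strategy, keeps more than 99.9%. If the planned test of CT colonography against direct colonoscopy pools the two colonoscopy arms, the comparison is 32% of 2,500 against (22.5% + 27.5%)/2 = 25% of 5,000, also above 99.9%. The telephone comparison is not singled out in the protocol as the main one, although the sample-size section does claim power for it.

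*Other features would lower power further.* Randomisation is by household and the participation rate counts eligible invitees only, so a reader might want to deduct for clustering and ineligibility as well. The documents give no figure for either, and neither bears on 32% against 35%. They do not belong in the restated power.

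**Conclusion.** The inconsistency is real and is visible within the article. At the FS rate that the protocol itself reports, the claim of more than 99% power holds for one of the two CT comparisons but not for the other: CT colonography against telephone-consultation colonoscopy has about 94%. The planned difference there shrinks from 7.5 to 4.5 points, and the comparison becomes the least powered of the three pairwise tests, below the 98% for consultation mode.

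The practical effect is modest. Power of 94% is still high, and the overall test and the other CT comparison are unaffected, so the documents do not support calling the trial underpowered. The result rests on 2,500 analysed per arm, 27.5% uptake in the telephone arm, independent individuals, and an unadjusted two-sided 5% pairwise test.

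**What to change.** In the Sample size section, take one of two routes:

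1. Plan with 32% for CT colonography and restate the power against telephone-consultation colonoscopy as about 94%, keeping above 99% for CT colonography against outpatient-consultation colonoscopy and for the overall test.
2. Keep 35%, state what it actually rests on (including any deliberate increase over the FS figure and the reason for it), and correct the attribution to FS.

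On either route, show power for CT colonography against telephone-consultation colonoscopy at both values: about 94% at 32% and 99.99% at 35%. The cost is a sentence or two and one less favourable power figure. Sample size, tests and outcome definitions stay as they are.

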## Discussion

The optimal screening test is still under debate. Stool-based tests and FS are considered as suboptimal tests. DCBE and capsule endoscopy are not recommended for CRC screening, because of its inferior diagnostic sensitivity.

Colonoscopy and CT colonography are the most accurate colonic exams and screening options by which inspection of the entire colon is allowed. Prospective data on the effectiveness (CRC mortality reduction) of population based screening programmes by colonoscopy and CT colonography are lacking. The effectiveness of a screening programme is directly influenced by the participation rate. It is expected that the participation rate of CT colonography screening is higher than with colonoscopy screening, because of the lower burden of the procedure. However, all CT colonography positives will need colonoscopy for confirmation and therapy or need surveillance which can lower the participation rate to the total CT colonography programme. It is not known to what extent this would influence participation rate.

This study will evaluate the efficacy of a colorectal cancer screening programme in the Netherlands using colonoscopy and CT colonography as a screening method. It will show whether participants are well-informed about the screening programme and what factors would influence (non-)participation. If this study shows that a prior consultation by telephone instead of a prior consultation at the outpatient clinic in colonoscopy screening has a positive effect on the participation rate, this would contribute to the effectiveness of future screening programmes.

This study will provide information on the uptake of a population screening by colonoscopy and CT colonography and on factors influencing the uptake. Furthermore, this study will give insight into concerns on CT colonography and especially on colonoscopy screening including burden of the procedures, risks and costs. As other screening options have already been investigated, this study will enable to determine the most cost-effective screening method for CRC in the Netherlands.

